### **IV-3. Study duration and dates**

The anticipated duration of recruitment is 12 months for step 1 and 12 to 24 months for step 2. The duration of participation of each patient is 6 months.

The total duration of the study is 18 to 42 months.

## V. STUDY POPULATION

### V-1. Inclusion criteria

Two patient populations will be included in the study: (1) unvaccinated elderly and high COVID-age population and (2) high-risk immunocompromised population.

#### V-1-1. Unvaccinated elderly and high COVID-age population:

1. SARS-CoV-2 RNA detected in a specimen, or positive antigenic test,  $\leq 7$  days after onset of symptoms
2. Symptoms of COVID-19 (so including but not limited to: fever; cough; breathlessness; chest pain; wheeze; sore throat; haemoptysis; runny nose; fatigue; muscle or joint pain; confusion; headache; seizures; nausea; vomiting; diarrhoea; abdominal pain; poor appetite; skin ulcers or rash; ear pain; conjunctivitis; anosmia; bleeding; lymphadenopathy). The attending clinician will determine if symptoms are consistent with COVID-19.
3. Clinical status not requiring admission to hospital for COVID-19 disease and oxygen support
4. Ability to transfuse (per randomisation) within 7 days after onset of symptoms
5. Men or women, 70 years or older  
OR  
under 70 years with significant comorbidities (arterial hypertension, diabetes, obesity, asthma or other chronic pulmonary disease, cardiovascular disease, cerebrovascular disease, chronic kidney disease / dialysis, liver disease, chronic neurological disease, rheumatoid arthritis, lupus or psoriasis) resulting in a 'COVID-age' of 70 years or more according to the ALAMA risk calculator <https://alama.org.uk/covid-19-medical-risk-assessment/>
6. Signed written informed consent

#### V-1-2. High-risk immunocompromised population

1. SARS-CoV-2 RNA detected in a specimen, or positive antigenic test,  $\leq 7$  days after onset of symptoms
2. Symptoms of COVID-19 (so including but not limited to: fever; cough; breathlessness; chest pain; wheeze; sore throat; haemoptysis; runny nose; fatigue; muscle or joint pain; confusion; headache; seizures; nausea; vomiting; diarrhoea; abdominal pain; poor appetite; skin ulcers or rash; ear pain; conjunctivitis; anosmia; bleeding; lymphadenopathy). The attending clinician will determine if symptoms are consistent with COVID-19.
3. Clinical status not requiring admission to hospital for COVID-19 disease and oxygen support
4. Ability to transfuse (per randomisation) within 7 days after onset of symptoms
5. Male or female with extremely high risk including:
  - a. Patients with at least one of the following acquired immune deficiencies:
    - i. Lymphoid malignancies treated within the last 12 months
    - ii. Lymphoid malignancies with persistent hypogammaglobulinaemia (IgG < 5g/L)
    - iii. Myeloid malignancies treated by chemotherapy within the last 12 months
    - iv. Myeloid malignancies treated by anti-BCL-2 drugs within the last 12 months
    - v. Myeloid malignancies associated with prolonged neutropenia ( $\geq 6$  weeks)
    - vi. Solid tumour undergoing treatment with chemotherapy (until 3 months after completion of the last chemotherapy cycle).
    - vii. Allogenic hematopoietic stem cell transplantation within the last 12 months or anytime if on-going treatment for chronic GVHD
    - viii. Organ transplantation

- ix. Anti - B (CD20/CD19) MoAb and/or mycophenolate mofetil treatment within the last 12 months
  - x. Anti-CD19/CD20 CAR-T cell treatment
  - xi. ATG or alemtuzumab treatment within the last 6 months
  - xii. AIDS
- or
- b. Patients with primary lymphoid immune deficiencies:
    - i. B cell deficiencies (such as Bruton agammaglobulinemia)
    - ii. T cell deficiencies (such as Wiskott Aldrich disease)
    - iii. Combined deficiencies (such as Common variable immunodeficiency )
- Or
- c. Patients without detectable seroconversion  $\geq 3$  weeks after complete vaccination schedule with an approved vaccine.
6. Signed written informed consent

## **V-2. Exclusion criteria**

### **V-2-1. Unvaccinated elderly and high COVID-age population:**

1. Age < 18 years
2. Prior or concurrent treatment for COVID-19 (unless listed as authorized specific treatment)
3. History of documented SARS-CoV-2 infection in the last 90 days prior to enrolment
4. Prior anti-SARS-CoV-2 immunization
5. Contraindication to receiving CCP including previous history of transfusion-related acute lung injury (TRALI) or moderate or severe allergic reaction to blood components
6. Known participant objection to receiving plasma products
7. Primary or acquired immune deficiency listed below (see cohort 2)
8. Refusal to participate expressed by patient or legally authorised representative
9. Pregnancy

### **V-2-2. High-risk immunocompromised population**

1. Age < 18 years (except for UK)
2. Prior or concurrent treatment for COVID-19 (dexamethasone, anti-IL-6/IL6R, remdesivir) except for prophylactic administration of anti-SARS-Cov2 monoclonal antibodies (pre or post exposure) in cohort 2 and authorized specific treatment
3. History of documented SARS-CoV-2 infection in the last 90 days prior to enrollment
4. Contraindication to receiving CCP including previous history of transfusion-related acute lung injury (TRALI) or moderate or severe allergic reaction to blood components
5. Known participant objection to receiving plasma products
6. Refusal to participate expressed by patient or legally authorised representative
7. Pregnancy

Any patient eligible for both cohorts will be included in cohort 2.  
Enrolment in other trials after reaching the primary end-point is authorised.

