#### **II-6. Experimental medicinal product and justification for dosage and dosage regimen**

Medicinal product: COVID-19 convalescent plasma (CCP)

Dosage: Two units (200 to 350 mL per unit) of high titre CCP.

Convalescent plasma should be derived by apheresis from vaccinated donors, collected at least 3 weeks post first dose of vaccine, who have had a previous laboratory confirmed SARS-CoV-2 infection.

Both sequences (first SARS-CoV-2 infection and subsequent vaccination as well as vaccination and subsequent SARS-CoV-2 infection) are acceptable as long as the antibody thresholds defined below are met in the collected CCP units.

As far as the availability of CCP units allows, the two plasma units should have been donated by two different convalescents. Plasma should contain a minimum neutralising antibody titre of 1:640 against delta (B.1.617.2), omicron, or any future variant as that would allow a titre of 1:100 to be achieved in an average recipient and this level is considered sufficient to neutralise the virus within host. Around 30% of vaccinated donors with a previous infection will demonstrate these antibody levels.

Before convalescent plasma is approved for clinical trial use, the SARS-CoV-2 antibodies should be measured from a donor prior to or during donation or from donated plasma after donation either using live virus neutralisation assay with delta variant, Elecsys Anti-SARS-CoV-2 S Assay (from Roche), Anti-SARS-CoV-2-QuantiVac-ELISA (IgG) (from Euroimmun) or other assay which have been demonstrated to predict the required titre level:

- Live virus microneutralisation assay: a minimum neutralising antibody titre of 1:640 against delta, omicron, or any future variant  
or
- Elecsys Anti-SARS-CoV-2 S (Roche): a minimum antibody concentration of 20.000 IU/ml  
Or
- Anti-SARS-CoV-2-QuantiVac-ELISA (IgG) (Euroimmun): a minimum antibody concentration of 4.000 BAU/ml  
or
- Any other assay shown to correlate with any of the above assays.

Lymphocytes isolated from a blood sample drawn from the pre-donation bag will be used for measuring anti-SARS-CoV-2 reactivity including variants.

Retention Plasma or a 5 mL serum sample from each convalescent plasma donation provided for clinical trial should be stored for further testing to allow comparison of data between countries and to analyze their cross-neutralization capacity against new viral variants which might evolve during the course of this trial.

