As mentioned earlier, an Ab dose effect has been reported with CCP transfusion. The transfusion of 2 units of plasma (the same day or on 2 subsequent days) is the maximum amount of plasma one can reasonably transfuse early after COVID-19 symptoms initiation and in an outpatient setting. Such a dosage of CCP has been applied in several clinical studies and found to be well tolerated.

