## **IV. STUDY DESIGN**

### **IV-1. Overall design**

COVIC-19 is a multicentre international, randomised, open-label adaptive superiority phase III trial to evaluate the efficacy and safety of COVID-19 convalescent plasma in the treatment of COVID-19. It is conducted in a harmonized approach in different countries in Europe.

The study is randomizing adult COVID-19 patients to one of two arms (1:1 ratio): standard of care or standard of care and very high neutralizing Ab titre convalescent plasma. Randomization will be stratified by centre and by patient cohort. The control group will receive 'standard care' therapy. Neither blinding nor placebo will be used to avoid unnecessary intravenous access.

Standard of care therapy may include anti-SARS-CoV-2 specific medication listed as authorized in a dedicated appendix. Centres should ensure that medications used as standard of care are used similarly for patients in both treatment arms.

Participating patients will be included in 2 cohorts of vulnerable patients (cohort 1: unvaccinated elderly ( $\geq 70$  years) and younger with comorbidities (cohort 1:  $< 70$  with comorbidities), cohort 2: immunosuppressed patients).

All subjects will undergo a series of efficacy and safety assessments, including laboratory assays. Subjects will be assessed at baseline, and at Days 3, 14, 28, 90 and 180.

Nasopharyngeal swabs (NP) or lower respiratory tract samples will be obtained at D1 (pre-treatment), and at D3, D14, D28 and D180 (and monthly in case of positivity until of clearance) for cohort 2 and on the day of hospitalization (if applicable).

Blood samples will be obtained at D1, D14 and D28 and on the day of hospitalization (if applicable).

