#### **VI-4. Data recorded**

##### **VI-4-1. Baseline information**

The following information will be recorded on the web-based form by the attending clinician or delegate:

| Data recorded                                                                                                                                     | Source of the data   |
|----------------------------------------------------------------------------------------------------------------------------------------------------------|-----------------------------|
| Medical history including High risk categories/major comorbidity                                                                                         | Patient and medical records |
| Patient details (age, sex...), place of residence, weight, height, BMI, Vital signs                                                                      | Medical records             |
| SARS-CoV-2 vaccination (dates, type of vaccine)(cohort 2 patients)                                                                                       | Patient and medical records |
| COVID-19: COVID-19 symptom onset date, Date of SARS-CoV-2 RNA detection, symptoms details, infection history, COVID-19 severity as assessed by WHO score | Patient and medical records |
| Concomitant medication (including use of any other medication to treat COVID-19 as standard of care)                                                     | Patient and medical records |
| ALAMA risk score                                                                                                                                         | Medical records             |
| Biological data                                                                                                                                          | Medical records             |

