### **VII-1. Investigational therapeutic**

The investigational medicinal product is composed of two plasma units provided by two COVID-19 convalescent patients, fully compliant with national regulations as detailed in the investigator's brochure.

The first unit of ABO compatible convalescent plasma (200 to 350 ml per unit) will be infused intravenously on study day 1 (as soon as possible after randomisation) and the second on day 1 or day 2. Plasma has been obtained by apheresis from donors who have recovered from COVID-19 infection (at least 14 days after recovery) and have been vaccinated (at least 3 weeks after first dose of vaccine). A combination of both a SARS-CoV-infection and a SARS-CoV-2 vaccination of the donor is required – irrespective of the sequence of infection and vaccination. As far as the availability of CCP units allows, the two plasma units should have been donated by two different convalescents.

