#### **VII-4. Administration**

Two convalescent plasma units of 200 to 350 ml will be transfused i.v. in patients from the CCP arm, on one or two days.

Process for administration of convalescent plasma is as follows:

- All administration bedside transfusion safety checks must be undertaken.
- The donation number, volume transfused, and start and finish date and time of transfusion should be documented.
- Any suspected serious adverse reaction to transfusion must be reported to the transfusion laboratory as well as being reported on trial documentation.

Convalescent plasma will be administered by staff trained to give transfusions of blood components and have been approved to do so per applicable regulation. All participants must be under surveillance during the infusion and should be monitored closely for 2 hours after the infusion. Plasma transfusion per- and post-transfusion surveillance as well as traceability and haemovigilance will be fully compliant with current regulations.

In hospital, CCP will be administered in day units. The exact logistics will vary depending on each hospital's layout. Home transfusion, as well as transfusion in long-term care facilities or in health centers with dedicated personal, will be considered as well.

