### **VII-9. Participant discontinuation/withdrawal from the study**

If a subject is withdrawn before completing the study, the reason for withdrawal will be entered on the appropriate eCRF. Whenever possible and reasonable, the evaluations that were to be conducted during the final study visit should be performed at the time of premature discontinuation.

It is vital to obtain follow-up data on any subject who terminated because of an AE. In any case, every effort must be made to ensure safety follow-up procedures are completed.

A decision by a participant (or their parent/guardian) that they no longer wish to continue receiving study treatment should not be considered to be a withdrawal of consent for follow-up. However, participants (or their parent/guardian) are free to withdraw consent for some or all aspects of the study at any time if they wish to do so. In accordance with regulatory guidance, de-identified data that have already been collected and incorporated in the study database will continue to be used (and any identifiable data will be destroyed). For participants who lack capacity, if their legal representative withdraws consent for treatment or methods of follow-up then these activities would cease.

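### Section V-2-2 admits UK cohort 2 patients under 18 with no age or weight floor, Section IV-1 says adults are randomised, and the two-unit plasma dose has no weight term

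*Protocol*

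**What the plan says.** **Who may enter.** Section IV-1 states: "The study is randomizing adult COVID-19 patients to one of two arms (1:1 ratio". The cohort 2 exclusion list in Section V-2-2 has "Age < 18 years (except for UK" as its first item. Cohort 1 (Section V-2-1) excludes everyone under 18 without exception. The cohort 2 inclusion criteria (Section V-1-2) define eligibility by immune status and give no age or weight limit. Section VII-9 covers "A decision by a participant (or their parent/guardian) that they no longer wish to continue receiving study treatment".

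**What they receive.** Section II-6 sets the dose: "Two units (200 to 350 mL per unit) of high titre CCP". Section VII-1 says that the first unit "will be infused intravenously on study day 1 (as soon as possible after randomisation) and the second on day 1 or day 2". Section VII-4 repeats it for the whole arm: "Two convalescent plasma units of 200 to 350 ml will be transfused i.v. in patients from the CCP arm, on one or two days". The justification in Section II-6 is that "2 units of plasma (the same day or on 2 subsequent days) is the maximum amount of plasma one can reasonably transfuse" to an outpatient early in the illness. The same section ties the titre threshold to an average recipient.

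**What is recorded.** The baseline data in Section VI-4-1 include "place of residence, weight, height, BMI, Vital signs". No eligibility or dosing rule in the protocol uses the weight.

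**The concern.** The overview and the operative criterion disagree about the population. The UK exception looks deliberate: cohort 1 has none, and Section VII-9 provides for a parent or guardian separately from the legal representative of someone who lacks capacity. So the word to correct is the one in Section IV-1.

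Once minors may enter, the dose needs to fit them. A fixed number of units delivers more volume per kilogram as weight falls. Section II-5-1 names circulatory overload among the known risks of plasma transfusion, and Section VII-4 allows transfusion at home or in long-term care as well as in day units. A dose justified as the most that can reasonably be given to an outpatient, without reference to body size, is carried over unchanged to a child of any weight. What is at stake is the safety of a small group, and whether a site or ethics reader can tell what that group would receive.

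**Working it through.** **Inputs.** Unit volume 200 to 350 mL and two units per patient (Sections II-6, VII-1, VII-4). Second unit on the same or the next day (Sections VII-1, VII-4). The protocol gives no body weights, so all weights w below are assumptions.

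**Step 1: the plan's total.** 2 × 200 = 400 mL and 2 × 350 = 700 mL.

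**Step 2: total per kilogram**, 400/w to 700/w. All of it may be given in one day.

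| Assumed weight | Total, mL/kg |
|---|---|
| 70 kg | 5.7-10.0 |
| 50 kg | 8.0-14.0 |
| 30 kg | 13.3-23.3 |
| 20 kg | 20.0-35.0 |

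**Step 3: ratio to a larger patient given units of the same size.** The ratio is W/w for a reference weight W. Against 70 kg: 70/30 = 2.3 and 70/20 = 3.5. Against 50 kg: 50/30 = 1.7 and 50/20 = 2.5. A minor of adult weight has a ratio of 1, so no extra concern arises there.

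**Step 4: let unit sizes differ.** The protocol does not require equal unit sizes. The pairing most favourable to the plan sets the smallest units for the child against the largest for a 70 kg adult (10 mL/kg): 13.3/10 = 1.3 at 30 kg and 20/10 = 2.0 at 20 kg. The smallest permitted total exceeds 10 mL/kg whenever 400/w > 10, that is, below 40 kg.

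**Step 5: split over two days.** The daily load becomes 200/w to 350/w: 6.7-11.7 mL/kg/day at 30 kg and 10-17.5 at 20 kg. At 20 kg with 200 mL units it is 200/20 = 10 mL/kg/day, equal to the top of the 70 kg one-day range. With equal unit sizes, the split daily load exceeds the 70 kg one-day figure when 70/(2w) > 1, that is, below 35 kg. With 200 mL units for the child and 350 mL units for the adult, it does so when 200/w > 10, that is, below 20 kg. The total over two days is as in Step 2.

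**Step 6: for scale only.** The total that matches the 70 kg figure per kilogram is 400w/70 to 700w/70: 171-300 mL at 30 kg and 114-200 mL at 20 kg. This is not a dosing proposal.

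**The case against.** **The rule may exist elsewhere.** This is the strongest point. The document is a core protocol for several countries, the exception is specific to the UK, and Section VII refers product details to the investigator brochure and the product circuit, neither of which is shown. A paediatric volume rule could sit there or in a UK document. That stands as a limit on the finding. However, the pointers in Sections VII and VII-1 do not mention minors, and Section VII-4 states the two-unit dose without qualification. If a rule exists, a cross-reference and a correction to Section IV-1 are still needed.

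**Eligibility is clear in practice.** Section IV-1 is an overview, and a site working from the exclusion list would not be misled about who may enter. That is fair, and it makes this half of the point editorial.

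**The volume is not fixed.** Correct: the number of units is fixed and the volume varies 1.75-fold between bags (700/400). A site could choose small units and split them. Nothing requires either, and nothing links the choice to weight.

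**Safeguards exist.** Contraindication to plasma is an exclusion in Section V-2-2. Section VII-4 requires bedside checks, trained staff, surveillance during the infusion and close monitoring for two hours afterwards. These help, but none limits volume by weight, and monitoring detects overload only after volume has been given.

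**Overload is rare.** Section II-5-1 reports 4.1 per 100,000 transfused plasma units in national haemovigilance data. The figure is not broken down by age or weight, so it neither settles nor raises the concern for small patients.

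**Conclusion.** The point holds as a minor safety and consistency matter. Section IV-1 conflicts with Section V-2-2. For UK cohort 2 minors, the protocol prescribes a dose with no body-size term and points to no rule that would supply one. Followed as written with equal unit sizes, it gives 2.3 times (30 kg) and 3.5 times (20 kg) the volume per kilogram of a 70 kg patient. These figures rest on assumed weights. The number of minors expected is not stated and may be very small.

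Three stronger readings are tempting, and the document supports none of them:

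- **That the protocol exposes children to an unsafe volume.** It gives no mL/kg limit, so the shown text cannot establish that any of these volumes is unsafe.
- **That there is a definite weight, such as 35 kg, below which splitting no longer helps.** The threshold moves between 20 and 35 kg with the unit sizes assumed, and the protocol leaves those open.
- **That the trial's result is affected.** The sample size and the test of the primary endpoint do not depend on this, and the primary comparison is untouched.

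**What to change.** 1. In Section IV-1, state that cohort 2 may include minors in the UK.
2. In Sections II-6, VII-1 and VII-4, limit the two-unit dose to adults or to patients above a stated weight.
3. For smaller UK minors, state either a weight-based volume or a minimum weight for inclusion, using the weight already collected at baseline under Section VI-4-1.
4. If such a rule already exists in the investigator brochure or a UK document, replace steps 2 and 3 with an explicit cross-reference in Sections V-2-2 and VII-4.

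The cost is a short amendment. A weight-based volume may mean part-unit transfusions at UK sites, and a minimum weight would exclude a few small minors. If the rule already exists, the cost is a cross-reference and the correction to Section IV-1.

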## **VI. STUDY ASSESSMENTS AND PROCEDURES**

### **VI-1. Screening Assessment**

Patients will be approached via their direct care team in hospitals, nursing homes, or General Practice in the following scenarios where symptoms compatible with COVID-19 are present: (1) Those attending routine appointment, (2) Those receiving unscheduled care in emergency or acute assessment units, but not requiring admission for COVID-19 (3) Those who contact their hospital, community team, or COVID-19 Core protocol

family practitioner reporting symptoms (4) High-risk asymptomatic patients who are screened for SARS-CoV-2 as part of routine care, in line with current clinical guidelines. Those with a positive virological result will become eligible on reporting symptoms.

